#### Participant discontinuation criteria

A participant will be considered discontinued from Component 1 if they do not attend the safeTALK workshop for any reason (including if they leave the workshop in the first 30 min). Participants who arrive more than 30 min late to the safeTALK workshop will miss important safety and wellbeing information, and will not be permitted to continue; they will also be considered discontinued from Component 1. Given that some students in Component 1 will also be participating in Component 2, all students regardless of their safeTALK completion will be asked to complete the subsequent questionnaires.

If a participant leaves the workshop early, a member of the study team will record how much of the workshop they completed and use this to determine whether the participant is considered “withdrawn”.

A participant will be discontinued from the study if they miss the T1 assessment. If a student consents but misses the baseline assessment, they may complete the baseline any time prior to T2, after which they will be discontinued.

A participant allocated to the intervention group in component 2 will be discontinued if:
Use of the intervention interferes with appropriate clinical management of risk of harm to self or others (as judged by the school wellbeing staff and/or senior researchers);Serious adverse events (SAEs; defined in section “Definitions of adverse events and serious adverse events”) occur that could be associated with the Reframe IT intervention;The participant or their parent or guardian indicates they no longer wish to use the Reframe IT intervention.

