#### Participant withdrawal criteria

A participant will be considered “withdrawn” from the study in cases where all involvement is ceased.

A participant will be withdrawn if:
Participation interferes with appropriate clinical management of risk of harm to self or others (as judged by the school wellbeing staff and/or senior researchers, and in consultation with treating clinicians if appropriate);SAEs occur that could be associated with any intervention included in this study;The participant or their parent or guardian indicates they no longer wish to participate;The participant leaves the school.

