#### Study discontinuation criteria

The study may be terminated by the Sponsor (Orygen) with or without cause.

Discontinuation will be considered in the event that a suicide attempt or death occurs, and it is *reasonably possible* that the attempt or death was caused by any of the interventional components (safeTALK, screening or Reframe IT) of the study. See section “Assessment and documentation of AEs”. for details on determination of causality.

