#### Screening for risk

The screening will take the form of self-report measures embedded into the questionnaires at each time point. Students who report suicidal ideation within the past 4 weeks (SIDAS score of 1 or higher) or any level of current suicidal ideation (single multiple-choice item) will be contacted by a member of the school wellbeing team or the research team, who will assess risk and refer them to appropriate support.

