### Outcomes and measures

#### Primary outcome

The primary outcome for this study is change in past 4-week suicidal ideation at T3 and T4 when compared to T2, assessed via the SIDAS [45]. The SIDAS is designed to screen individuals in the community for presence of suicidal thoughts and assess the severity of these thoughts. It comprises five items, each targeting an attribute of suicidal thoughts: frequency, controllability, closeness to attempt, level of distress associated with the thoughts and impact on daily functioning. Responses are measured on a 10-point scale. Total SIDAS scores are calculated as the sum of the five items, with controllability reverse scored (10 = 0, 9 = 1,…, 0 = 10), with total scale scores ranging from 0 to 50. Items are coded so that a higher total score reflects more severe suicidal thoughts.

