### Statistical analyses

#### Component 1

For each continuous outcome, changes over time will be assessed using linear mixed effects modelling with school included as a random factor. This analysis will examine whether there is a trend over time and whether the trend is linear or non-linear. Change in current suicidal ideation between T1 and T2 will be assessed using the McNemar–Bowker symmetry test for nominal data.

#### Component 2

Descriptive statistics will be used to compare participant characteristics between the study arms, and to assess for any imbalance.

The analysis will adopt the intention-to-treat approach, which is to include in the analysis all participants who have been randomised and regard each participant as belonging to the randomised group concerned irrespective of protocol adherence. Difference in change in the primary outcome of SIDAS score between the treatment groups will be examined using linear mixed effects modelling with the treatment group as a fixed factor and school included as a random factor. Secondary outcome measures will be similarly analysed. As a secondary analysis, compliance (as measured by the number of modules completed) and other potential covariates (e.g. gender) will be accounted for.

If the amount of missing data is non-trivial, multiple imputation will be considered to handle the missing data.

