##### Serious adverse event (SAE)

An SAE is any untoward medical occurrence that:
Results in death;Is life-threatening;
Life-threatening in the definition of serious refers to an event in which the participant was at risk of death at the time of the event; it does not refer to an event which hypothetically might have caused death if it were more severe.Requires inpatient hospitalisation or prolongation of existing hospitalisation;Results in persistent or significant disability/incapacity;Is a congenital anomaly/birth defect;Is an important medical event that although not immediately life-threatening or result in death or hospitalisation, based upon appropriate medical and scientific judgement, may jeopardise the participant and/or require intervention to prevent one of the outcomes listed above.

Outpatient treatment in an emergency department is not in itself an SAE, although the reasons for it may be (e.g. suicide attempt).

Hospital admissions and/or surgical procedures planned before or during a study are not considered SAEs if the illness or disease existed (or the surgery was planned) before the participant was enrolled in the study, provided that it did not deteriorate in an unexpected way during the study.

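### The SAE withdrawal rule contains the SAE rule for stopping Reframe IT, so an SAE possibly linked to Reframe IT ends remaining SIDAS collection and not only the intervention (minor)

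*Protocol article*

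**What the plan says.** Under Participant discontinuation criteria, a student allocated to Reframe IT is discontinued if SAEs "occur that could be associated with the Reframe IT intervention". Under Participant withdrawal criteria, any participant is withdrawn if "SAEs occur that could be associated with any intervention included in this study". Withdrawal is defined there as applying "in cases where all involvement is ceased". Both rules are worded as mandatory, and the article states no precedence between them.

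Study discontinuation criteria shows what counts as an intervention, referring to "any of the interventional components (safeTALK, screening or Reframe IT) of the study". Screening for risk describes screening as "self-report measures embedded into the questionnaires at each time point".

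The primary outcome is change in SIDAS at T3 and T4 relative to T2. Under Statistical analyses, the Component 2 analysis is by intention to treat and is to "include in the analysis all participants who have been randomised".

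**The concern.** A two-tier scheme is useful only if some events stop the treatment while leaving the assessments in place. For SAEs the upper tier absorbs the lower one, so that option is never available. If the rules are followed as written, the primary outcome stops being collected in a student who has just had a serious event possibly caused by the treatment under test.

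These are not random losses. The SAE section says that emergency outpatient treatment is not in itself an SAE, "although the reasons for it may be (e.g. suicide attempt"), and the five SIDAS attributes are "frequency, controllability, closeness to attempt, level of distress associated with the thoughts and impact on daily functioning". The event that triggers withdrawal can therefore bear directly on the score that goes missing. T4, the later of the two assessments at risk, is the time point used for the power calculation. An analysis plan can model missing scores, but it cannot recover scores that a conduct rule stopped anyone from collecting.

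Two further features matter. An SAE attributed to Reframe IT can arise only in the Reframe IT arm. The attribution is a judgement by a study team member (Assessment and documentation of AEs), and team members other than the statistician know the allocation (Randomisation and treatment allocation).

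**Working it through.** **Comparing the two lists.** The discontinuation list for Reframe IT students and the withdrawal list share three paired criteria.

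| Criterion | Discontinuation (Reframe IT arm) | Withdrawal (any participant) | Distinct? |
|---|---|---|---|
| Clinical management | use of the intervention interferes | participation interferes | yes |
| Wishes of student or parent | no longer wants Reframe IT | no longer wants to take part | yes |
| SAE | could be linked to Reframe IT | could be linked to any study intervention | no |

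Reframe IT is one of the study interventions, so SAEs possibly linked to Reframe IT are a subset of SAEs possibly linked to any study intervention. Whenever the first SAE rule applies, the second applies too. Only this pair collapses, which suggests a drafting slip.

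**Does other text keep SIDAS going?** The sentence that keeps questionnaires running, under Participant discontinuation criteria, concerns students who did not complete safeTALK. Voluntary discontinuation provides for follow-up of the adverse event, not of SIDAS. Nothing else addresses the case. The loss of SIDAS is inferred from the definition of withdrawal; the article does not state it in those words. Reframe IT runs between T2 and T3, so an event during treatment costs T3 and T4, and an event after T3 costs T4 only.

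**Size.** The plan has no figure of its own to reproduce, and no SAE rate is given. The following is an illustration.

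- From Sample size and power calculation and the 1:1 allocation: 335 randomised, so 335 / 2 = 167.5 per arm; drop-out 20%; planned SIQ difference 14.5 on a 0–180 scale. SIDAS runs from 0 to 50.
- Assumed: k = 0 to 3 extra withdrawals caused by the Reframe IT trigger; d = 5 to 20 points by which these students' later SIDAS exceeds what their own earlier scores predict.
- Formula: if the analysis in effect replaces each missing score by its prediction, the shift in the arm mean is (k / 167.5) × d.

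Results:

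- k = 0: no shift.
- k = 1: 0.00597 × 5 to 20 = 0.03 to 0.12 points.
- k = 3: 0.01791 × 5 to 20 = 0.09 to 0.36 points.

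If 20% of these students would have been lost anyway, multiply by 0.8: 0.02 to 0.10 points for k = 1 and 0.07 to 0.29 for k = 3.

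Rescaling the planned difference by range, itself an assumption, gives 14.5 × 50 / 180 = 4.03 SIDAS points. Before the 0.8 factor, one extra withdrawal is 0.7% to 3.0% of that and three are 2.2% to 8.9%.

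**The case against.** The strongest reply is that ending all research contact with a minor after a possibly intervention-related SAE is a defensible protective choice in an ethics-approved protocol, since T3 and T4 repeat the suicide items in class groups at school. That stands as a reason for clinical discretion. It is weaker as a reason for automatic withdrawal: the withdrawal list already allows removal when participation interferes with clinical management, and the T3 and T4 responses are themselves triggers for the safety protocol, so withdrawal also removes a check on the student.

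A second reply is that few SAEs would be linked to Reframe IT alone. Every student is screened repeatedly and the threshold is only a possible association. This stands, and it shapes the fix: if a possible link to screening still forced withdrawal, amending the Reframe IT part would change little.

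Third, the numbers are assumed, and the pilots reported no iatrogenic effects (Indicated approaches), so zero extra withdrawals is plausible. Students with an SAE may also be lost at a higher rate than 20% under any rule, and after a death there is nothing to collect. All of this stands.

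Fourth, the full protocol and the safety committee's manual are not shown and may set a precedence. That limits certainty about practice, but the article's two mandatory rules still conflict as written.

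A reader might infer that the plan breaks intention to treat. It does not: withdrawn students stay in the analysis set, their earlier scores can be used, and multiple imputation is foreseen. A reader might also infer that the loss falls on one arm only. It does not: controls also receive safeTALK and screening and can be withdrawn under those triggers. Only the Reframe IT trigger is one-sided.

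**Conclusion.** The containment is established from the text: an SAE that could be associated with Reframe IT requires full withdrawal and ends any T3 or T4 SIDAS collection still to come. The resulting loss is outcome-related and partly specific to the intervention arm. Its frequency cannot be derived from the documents, and its effect on the primary contrast is probably very small, at most a few tenths of a SIDAS point under the assumptions shown.

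It would be tempting to conclude that the trial is biased in favour of Reframe IT. The documents do not support that. Such a bias needs both extra losses in the Reframe IT arm from this trigger and later scores in those students worse than their earlier SIDAS predicts; the documents establish neither. Severity: minor. It is worth correcting because the change is cheap and the students concerned are among the most informative about harm, which the trial also sets out to assess.

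**What to change.** Replace the automatic SAE line in the withdrawal criteria. An SAE possibly associated with a study intervention should stop the implicated intervention (Reframe IT, safeTALK or both), while T3 and T4 questionnaires continue if student and parent consent stands and the clinical team agrees.

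Reserve full withdrawal for three situations: continued participation, including the questionnaires themselves, is judged clinically unsafe (the first existing withdrawal criterion covers this); consent is withdrawn; or the student leaves the school. A mere possible link to screening should not trigger withdrawal automatically. Report SAE-related discontinuations and withdrawals by arm.

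The cost is a short protocol amendment with the ethics notification or approval that Changes to the protocol requires, and continued questionnaires for a few students under clinical oversight.

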#### Study discontinuation criteria

The study may be terminated by the Sponsor (Orygen) with or without cause.

Discontinuation will be considered in the event that a suicide attempt or death occurs, and it is *reasonably possible* that the attempt or death was caused by any of the interventional components (safeTALK, screening or Reframe IT) of the study. See section “Assessment and documentation of AEs”. for details on determination of causality.

### Recruitment

#### Recruitment of schools

Pending approval from their regulating authorities, all mainstream secondary schools located in the study catchment area with year 10 students enrolled will be invited to participate via letters of invitation and direct contact from the research team.

#### Recruitment of students

##### Component 1

All students in year 10 (or year 11, where applicable) at participating schools will be invited to participate. Students will be informed about the study in a number of ways, including announcements at assembly, letters to parents, parent and student information evenings, and participant information sheets. They will receive a full explanation of the aims of the study, the potential discomfort, risks, and benefits of taking part. It will be explained that the study is for research purposes and may provide benefit to the individual and that they can withdraw from the study at any time. Participants will also be asked to provide additional consent for the use of their data for future research. The use of their data for future research is optional, so participants may still take part in the current study without consenting to their data being used in future research projects. Participants will be notified that any future research projects wanting to use their data will have to be reviewed and approved by a recognised HREC. Written consent will be required from students, plus parents or legal guardians, prior to participation at T1, through completion of a study consent form. [See Additional file 5 for a sample Participant Information and Consent Form (PICF)]. The participant will be given a copy of the signed PICF to retain.

##### Component 2

Eligible students will be invited to participate either by a school counsellor or a member of the research team. Students and their parents or guardians will be required to sign a separate PICF, within 2 weeks of the baseline assessment.

### Procedure

Participants will be assessed at four time-points: baseline (T1), 2 weeks post-baseline (T2), 12 weeks post-baseline (T3), and 24 weeks post-baseline (T4). The T2 assessment will be completed immediately following participation in the safeTALK workshops, and T3 at the end of the Reframe IT intervention period (see Table 1).

**Table 1 Tab1:** Schedule of assessments and interventions

Time point		Study period				
	− T1	T1	T2		T3	T4
		Baseline Week 1	Week 3	Weeks 4–12	Week 12	Week 24
**Enrolment:**						
Informed Consent—safeTALK	X					
Inclusion/Exclusion Criteria—Reframe IT		X				
Informed Consent—Reframe IT			X*			
**Intervention administered:**		**Screening**	**safeTALK**	**Reframe IT** (one module per week)		
**Assessments:**						
Demographics		X				
Purpose-designed 3-item questionnaire assessing exposure to suicide and suicide prevention training		X				
Suicidal Ideation Attributes Scale (SIDAS)		X	X		X	X
Single item measuring current suicidal ideation		X	X		X	X
Youth Risk Behaviour Survey (YRBS)—suicide items		X	X		X	X
Patient Health Questionnaire-9 (PHQ-9)		X	X		X	X
Distress Questionnaire-5 (DQ-5)		X				
Hopelessness Scale for Children (HSC)		X	X		X	X
Negative Problem Orientation Questionnaire (NPOQ)		X	X		X	X
Resource Use Questionnaire (RUQ), adapted from the Young Mind Matters Service Use questionnaire (BRIEF VERSION)		X				
Resource Use Questionnaire (RUQ), adapted from the Young Mind Matters Service Use questionnaire (FULL VERSION)			X		X	X
Purpose-designed questionnaire asking about previous help-seeking behaviour and future help-seeking intentions from family, friends and other “informal” sources of help		X	X		X	X
4-item measure of attitudes towards help-seeking from adults at school, derived from the previous US Sources of Strength (SOS) trial and currently being used in the Australian SOS trials		X	X		X	X
4-item measure assessing attitudes towards overcoming secrecy barriers, derived from the previous US Sources of Strength (SOS) trial and currently being used in the Australian SOS trials		X	X		X	X
Willingness to Intervene Against Suicide Questionnaire (WIS)		X	X		X	X
Stigma of Suicide Scale (SOSS)—short form		X	X		X	X
Literacy of Suicide Scale (LOSS)—short form		X	X		X	X
Child Health Utilities Index 9 Dimension (CHU9D)		X	X		X	X
Purpose-designed 7-item questionnaire assessing acceptability of safeTALK training			X			
Purpose-designed 11-item questionnaire assessing acceptability of the Reframe IT intervention (or of not receiving it)					X	
Two items from the Patient Health Questionnaire-4 (PHQ-4), measuring anxiety		X				
Purpose-designed 11-item scale measuring experimentally induced distress, adapted from Yeater, Miller, Rinehart and Nason (2012)						X

***Note. Informed consent for Reframe IT participation and evaluation will be collected from eligible participants between Times 1 and 2, prior to randomisation and commencement of the Reframe IT intervention

Assessments will take the form of self-report questionnaires, and where possible will be collected using a computer or tablet employing REDCap (Research Electronic Data Capture), a secure, web-based data capture application hosted at The University of Melbourne [43, 44]. Where questionnaires are completed on paper, these will be later entered into REDCap by a member of the research team. Assessments will be completed at school in class groups, facilitated by a researcher, and supervised by a school staff member.

The REDCap system will automatically flag any participants who score between 1 and 20 on the SIDAS, as 1 is the established cut-off score indicating any level of suicidal ideation in the past month [45]. In the case that participants are required to complete paper versions of the questionnaire, they will be asked to include their full name on a separate detachable cover sheet. After the survey is completed, research staff will manually check their scores on the SIDAS instrument.

Within five school days of the baseline assessment, the research team will contact students who score between 1 and 20 on the SIDAS and conduct a brief semi-structured interview to determine eligibility for Component 2. Eligible students will be invited to participate and those who are interested will be given a consent form to be signed. They will then be randomised to either the intervention (Reframe IT) or control group (see below). A member of the research team will inform the relevant school staff member of the outcome of the randomisation.

Two weeks after the baseline assessment, safeTALK workshops will be delivered to all participating students. Immediately following the workshop, students will complete the T2 questionnaire. Students randomised to receive the Reframe IT intervention will complete the eight modules in the 10 weeks between T2 and T3 (i.e. approximately one module per week plus two additional weeks to allow for disruptions such as school holidays). Both T3 and T4 assessments will occur during class time; T4 will occur 12 weeks after T3. Researchers will be present at T3 and T4 assessment points if deemed appropriate by the research team and/or if requested by the school (e.g. they perceive a need for additional administrative support). No biological samples will be collected.

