### Aims and hypotheses

This project aims to evaluate the effectiveness of an integrated programme comprising universal, selective, and indicated components in reducing suicide risk, improving risk recognition, and increasing health service use among young people across North West Melbourne. Secondary aims are to evaluate the programme’s safety and cost-effectiveness. The programme involves the delivery and evaluation of universal educational workshops (safeTALK) to school students plus screening students for suicide risk (universal and selective approaches; Component 1), and the evaluation of online CBT (Reframe IT) delivered to students identified as being at risk (indicated approach; Component 2). Several hypotheses have been generated relating to each of the project components as well as the project as a whole.

It is hypothesised that completion of the safeTALK workshop will be associated with increased intentions to intervene with a suicidal person, higher levels of suicide literacy, higher levels of perceived behavioural control regarding intervening with a suicidal person, and reduced stigma towards suicide and suicidal behaviour.

It is hypothesised that the screening will lead to the identification of students at risk of suicide-related behaviour who had not previously sought help.

It is hypothesised that, compared to the control group, students in the Reframe IT intervention group will demonstrate reduced suicidal ideation, reduced symptoms of depression, reduced hopelessness, and improved problem-solving.

It is hypothesised that the project as a whole will lead to increased health-service use; increased help-seeking from informal sources; and improved attitudes towards help-seeking.

Finally, it is hypothesised that the programme will be cost-effective and have no iatrogenic effects.

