Change in health service use from formal and informal sources at T2, T3, and T4 when compared to T1 will be assessed using the Resource Use Questionnaire (RUQ) and a purpose-designed measure respectively. The RUQ was adapted from the Young Mind Matters Service Use questionnaire [51] and assesses use of mental health professionals and services, mental health-related hospitalisations, medication use for mental health reasons, and school-based mental health services. These data will also be used for the economic evaluation.

Change in attitudes towards seeking help from adults at school, and attitudes towards overcoming secrecy barriers, at T2, T3, and T4 when compared to T1, will be assessed using scales derived from the previous US Sources of Strength trial [52] and used in the Australian Sources of Strength trial [5]. Items are rated from 1 (strongly disagree) to 4 (strongly agree). Items on these scales are summed, with higher scores reflecting more positive attitudes towards help-seeking from adults at school, or more positive intentions to get help for suicidal friends and resist requests for secrecy.

Change in perceived ability and intention to intervene with a suicidal person at T2, T3, and T4 when compared to T1 will be assessed using the Perceived Behavioural Control and Intention subscales of the Willingness to Intervene Against Suicide Questionnaire (WIS) [53]. The scales have 20 and 22 items respectively. Both are rated on a 5-point scale ranging from 1 (“strongly disagree”) to 5 (“strongly agree”). Items 1, 3, 5, 10, 14, and 16 on the Perceived Behavioural Control subscale and items 12, 18, 19, 20, and 21 of the Intentions subscale are reverse-scored. The potential range of scores is 20–100 and 22–100 respectively; a higher score indicates a higher endorsement of intervening.

Change in stigma towards suicide at T2, T3, and T4 when compared to T1 will be assessed using the Stigma of Suicide Scale (SOSS)—Short Form [54]. This measure contains 16 one- or two-word descriptors of people who die by suicide, and respondents are asked to rate their level of agreement with each item on a 5-point scale ranging from 1 (“strongly disagree”) to 5 (“strongly agree”). The mean response to all items is calculated to score this instrument, with higher mean scores indicating greater suicide stigma.

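### Change in formal service use from T1 compares a brief questionnaire at T1 with a full one at T2–T4, so instrument version is confounded with time in the single-group contrast

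*Protocol article*

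**What the plan says.** Table 1 (Schedule of assessments and interventions) has two separate rows for the Resource Use Questionnaire. The row "Resource Use Questionnaire (RUQ), adapted from the Young Mind Matters Service Use questionnaire (BRIEF VERSION") is marked at T1 and nowhere else. The row "Resource Use Questionnaire (RUQ), adapted from the Young Mind Matters Service Use questionnaire (FULL VERSION") is marked at T2, T3 and T4 and not at T1.

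The Secondary outcomes section defines the outcome as "Change in health service use from formal and informal sources at T2, T3, and T4 when compared to T1", which "will be assessed using the Resource Use Questionnaire (RUQ) and a purpose-designed measure respectively". The RUQ thus covers formal sources and the purpose-designed measure covers informal ones. The section says that the RUQ "assesses use of mental health professionals and services, mental health-related hospitalisations, medication use for mental health reasons, and school-based mental health services", and does not distinguish the two versions or give a recall period for either.

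Aims and hypotheses states that "the project as a whole will lead to increased health-service use; increased help-seeking from informal sources". Under Study design, Component 1 is an uncontrolled before-and-after series. Under Statistical analyses, its continuous outcomes are examined for a trend over time in a linear mixed model with a random effect for school.

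**The concern.** A change score needs the same quantity measured at both ends. Here no RUQ version is used both at T1 and at any later time, so every contrast of a later time with T1 is also a contrast of one form with another. If the two forms pick up use differently, or ask about periods of different length, the difference enters the estimate directly and looks like a change in behaviour.

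In a randomised comparison such an effect would fall equally on both arms. The whole-programme hypothesis has no such protection, because every participating student is offered screening and safeTALK and there is no untreated group over the same period. At stake is whether the trial can say anything about one of its stated programme-level hypotheses. Part of the problem lies in data collection: items not asked at T1 cannot be recovered by analysis.

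**Working it through.** The plan gives no figure for this outcome, so there is none to reproduce. The check compares the schedule with the outcome definition, then gives an illustration of size.

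**1. Which measures are the same at T1 and later (Table 1)**

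| Measure | T1 | T2 | T3 | T4 |
|---|---|---|---|---|
| RUQ, brief | X | | | |
| RUQ, full | | X | X | X |
| Informal help-seeking questionnaire | X | X | X | X |

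The help-seeking attitude scales, WIS, SOSS, LOSS and CHU9D also appear as one instrument at all four times. Formal service use is the only T1-based change outcome whose instrument switches.

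**2. Can the model separate version from time?** Version is a function of time: brief if T1, full otherwise. An indicator for version equals an indicator for T1 versus later, so the two cannot both be estimated in a T1 contrast. Looking for non-linearity does not help. A pure version effect would appear as a step between T1 and T2, but so would a real early effect of screening and referral.

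**3. Recall window.** Assessments fall at 0, 2, 12 and 24 weeks after baseline (Procedure), so the gaps are 2, 12 − 2 = 10 and 24 − 12 = 12 weeks. If the full form asks about use since the last assessment, the window differs at every time point. For comparison, Additional measures gives the YRBS items a window of 12 months at baseline and the time between assessments thereafter. No window is given for the RUQ.

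**4. Illustration of size.** None of these assumptions is in the documents, except that 4020 is the planned number screened:

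- true use p is constant, so there is no real change;
- the T1 form records a share s of the users that the later form records;
- there is 3% random disagreement each way;
- the test is a paired McNemar test at two-sided 5%;
- clustering and attrition are ignored.

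With u = p(1 − s) + 0.03, v = 0.03 and d = u − v,

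P(significant rise) = Φ{[d√N − 1.96√(u + v)] / √(u + v − d²)}.

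For p = 0.20, s = 0.90, N = 4020: u = 0.05, v = 0.03, d = 0.02. The numerator is 0.02 × 63.40 − 1.96 × 0.2828 = 1.268 − 0.554 = 0.714. The denominator is √(0.08 − 0.0004) = 0.2821. The ratio is 2.53, so P = 0.99.

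| N pairs | True use | s = 0.95 | s = 0.90 | s = 0.80 |
|---|---|---|---|---|
| 4020 | 10% | 0.24 | 0.67 | 0.99 |
| 4020 | 20% | 0.67 | 0.99 | about 1.00 |
| 4020 | 30% | 0.94 | about 1.00 | about 1.00 |
| 1000 | 20% | 0.22 | 0.61 | 0.98 |

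With no version effect (d = 0) the value is Φ(−1.96) = 0.025. The formula is symmetric in u and v. If it is the later form that records the share s of the users recorded at T1, for example because T1 looks back further, the same probabilities apply to a significant fall.

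**The case against.** The strongest reply is that the content of the brief form is not shown. RUQ data also feed the economic evaluation, so the full form may only add costing detail to the same use/no-use questions. If the core items and recall period match, a contrast on those items is already like for like. Item content and scoring are commonly left to a fuller document. This stands as a limit: the article establishes a version switch that it does not address, not a demonstrated bias. It does not dispose of the point, because the article itself fixes both the schedule and the T1 contrast and says nothing that limits the contrast to shared items.

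Three stronger readings are tempting and are not supported.

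- A reader might infer that the artefact must favour the hypothesis, since a longer form prompts more recall. Neither content nor recall period is given, and a longer look-back at T1, as the YRBS items have, would push the other way.
- A reader might infer that the whole service-use outcome is affected. The informal-source measure is unchanged at all four times.
- A reader might infer that the randomised comparison or the within-trial cost comparison is biased. Both arms receive the same form at each time, so version does not bias the difference between them, and T2 to T4 use one form throughout. The T1 value is simply not a like-for-like baseline.

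It is also fair to say that the illustration mainly shows that a large sample detects a small difference, and that 4020 complete pairs is optimistic.

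**Conclusion.** The point holds for formal service use measured by the RUQ against T1. In the single-group contrast behind the whole-programme hypothesis, instrument version, and possibly recall window, is fully confounded with baseline versus follow-up. An observed rise or fall therefore could not be attributed to the programme rather than to the form.

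Its size cannot be determined from the article. The illustration shows only that, at the planned scale, a shortfall in capture of 5% to 10% can be enough for a significant result without real change, under assumed levels of use and disagreement and ignoring clustering and attrition.

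This is one secondary outcome. The SIDAS primary outcome and the sample size are untouched. It deserves correction because it carries a stated hypothesis and the remedy is cheap.

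**What to change.** 1. At T1, ask the same core use items as at T2–T4, with a comparable recall period.
2. In all schools, limit every contrast with T1 to items identical in both versions, expressed per unit of recall time. This works for counts of contacts. A yes/no item on any use needs equal windows, because such a proportion does not scale with the length of the window.
3. Keep the remaining full-form items for T2–T4, between-arm and cost analyses.
4. State the common items, their recall periods and this restriction in Secondary outcomes.

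Steps 1 and 2 belong together. Schools join in batches, so changing the T1 form only in schools not yet assessed would split the baseline instrument by batch unless the common-item rule also applies everywhere.

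The cost is a slightly longer T1 questionnaire or, where T1 has already been collected, a change outcome confined to the common items.
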